Since fibromyalgia involves a dysregulation of the autonomic (high sympathetic tone) and immune (enhanced pro-inflammatory activity) systems [25,41], non-invasive tVNS is expected to improve the symptoms of fibromyalgia, including chronic, musculoskeletal, and generalized pain [42,43], through modulation of the vegetative and immune systems [44]. The main objective of this intervention study is to evaluate the effects of repeated sessions of tVNS on pain and other symptoms in fibromyalgia patients, comparing auricular and cervical tVNS protocols which have been probed in other pathologies [45,46,47,48,49]. According to the effectivity reported in these studies, we hypothesize that a multi-session auricular and cervical tVNS protocol carried out under safety standards will provide analgesic and therapeutic effects in fibromyalgia patients, in comparison with sham and axillary nerve stimulation controls, and secondarily will also normalize the autonomic (via heart rate variability) and immune (via pro-inflammatory cytokine levels) functions supposedly altered in this disease.

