Sample size calculation will be based on the hypothesized significant differences between (auricular vs. cervical vs. sham vs. axillary) and within (baseline vs. post-intervention) groups. We conducted an a priori calculation of the sample size by the GPower statistical power analysis tool (3.1.9.2) for a mixed-model repeated-measures ANOVA (with groups and pre/post-intervention measures as levels of the between-group and within-group factors) [50], as a primary outcome parameter conducted for the pain questionnaire (BPI). Because the main parameter of interest for this calculation is the interaction between the factors group and measure, we conducted the analysis for the within–between interaction, setting the following input parameters: effect size (f) = 0.2 (medium size), α value = 0.05, Power (1-ß) = 0.95, number of groups = 4 (pooled sham, axillary stimulation, cervical tVNS, and auricular tVNS), number of measurements = 2 (baseline as pre-intervention, and at the end of the intervention), correlation for repeated measures = 0.5, and with nonsphericity correction (1). The output parameters were: non-centrality parameter = 17.92, critical F = 2.68, actual power 0.951, and total sample size = 112. Taking into account these estimates and adding 20% to the calculated sample to compensate for possible dropouts, we will include 34 patients per group (total sample size of 136).

Written informed consent (available in Supplemental material) will be provided by all patients prior to their participation in the study. The clinical trial will be submitted for consideration and approval by the Regional Ethics Committee for Clinical Studies. In accordance with national legislation (93/42/EEC and RD 1090/2015), the study will be pre-registered in the Spanish registry of clinical studies (https://reec.aemps.es/reec/public/web.html#, accessed on 28 December 2021). The study complies with the code of Ethics of the World Medical Association Declaration of Helsinki (amend 64th, 2013).

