### 2.6. Statistical Analysis

To exclude differences of baseline measurements (BPI scores as primary outcome measure, and FIQR, PGIC, PSQI, and BDI scores as secondary outcome measures) between groups, a mixed model 4 × 4 ANOVA will be used, with one between-group factor with four levels (4 groups), and one within-subject factor (four baseline measurements). A mixed model 4 × 8 ANOVA, with one between-group factor with four levels (four groups) and one within-subject factor (8 measurement days), will be used to analyze the scores of the outcome measures obtained in each of the questionnaires throughout the study (intra-intervention and follow-up period). In case of significant results of the ANOVAs, exploratory Bonferroni-corrected post-hoc *t*-tests will be conducted. A univariate analysis by a Chi-square test will be performed to explore the success of blinding with regard to the intervention, and *t*-tests as well as Chi-square tests will be conducted to exclude demographic differences (gender, age, and years of education) between groups. Pearson’s correlation coefficient (Pearson’s *r*) will be calculated for each tVNS group to analyze possible correlations between vagal activity measures (heart rate variability) during the intervention and questionnaire scores (FIQR, BPI, PGIC, PSQI, and BDI), as well as between pre- and post-intervention pro-inflammatory cytokines levels and outcome measures. The critical level of significance for all statistical analyses will be set to *p* < 0.05. The analyses will be carried out using the SPSS statistical software package.

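### Post-hoc t-tests use single-step Bonferroni; Holm's step-down version holds the same 5% familywise error and finds more of the tVNS-versus-control differences (optional, low priority)

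*Protocol article*

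**What the plan says.** Section 2.6 analyses the questionnaire scores with a mixed 4 × 8 ANOVA (four groups, eight measurement days). It then states: "In case of significant results of the ANOVAs, exploratory Bonferroni-corrected post-hoc" t-tests. It does not say how many comparisons form the family, which ANOVA term triggers them, or whether they are made per day or over days.

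The sample-size paragraph in section 2.1 defines the groups as "number of groups = 4 (pooled sham, axillary stimulation, cervical tVNS, and auricular tVNS" and sizes the trial on the group-by-measure interaction, not on any pairwise contrast. The Introduction states the hypothesis that auricular and cervical tVNS will have analgesic and therapeutic effects "in comparison with sham and axillary nerve stimulation controls".

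**The concern.** A four-group F-test cannot say which arm differs from which control. In section 2.6 only the post-hoc t-tests can. The hypothesis in the Introduction names two kinds of control, and the Discussion and Conclusions rest the claim of vagal specificity partly on the axillary group. To support that claim fully, a given tVNS arm has to win two contrasts, so power for the second and later rejections matters.

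That is where single-step Bonferroni is weakest. It holds every comparison to 0.05/k, however many others have already been rejected. Holm tests the smallest p-value at 0.05/k, the next at 0.05/(k−1), and so on, with the same familywise guarantee under any dependence between the tests. What is at stake is some avoidable loss of power in these comparisons, not a false-positive risk.

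**Working it through.** **1. The plan's own figure.** Inputs from section 2.1: "effect size (f) = 0.2 (medium size", "α value = 0.05, Power (1-ß) = 0.95, number of groups = 4", "number of measurements = 2 (baseline as pre-intervention, and at the end of the intervention" and "correlation for repeated measures = 0.5, and with nonsphericity correction (1".

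- Noncentrality: λ = f²·N·m/(1−ρ) = 0.04 × 112 × 2/0.5 = 17.92.
- With 3 and 108 degrees of freedom, critical F = 2.689 and power = 0.9513.

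This agrees with the stated output, "non-centrality parameter = 17.92, critical F = 2.68, actual power 0.951, and total sample size = 112" (the critical F is truncated there). So 112/4 = 28 evaluable patients per group; 28 × 1.2 = 33.6, rounded up to 34 randomised.

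**2. Translation to a pairwise difference.** For two measurements, the interaction test is a one-way F-test on the pre/post change. Its effect size on the change scale is f × √(m/(1−ρ)) = 0.2 × √4 = 0.4. If both controls share one mean and both tVNS arms share another, the standard deviation of the four means is half the difference, so the difference is 2 × 0.4 = 0.8 SD of change. Equal tVNS arms match the Abstract's prediction of no significant difference between the two protocols; equal controls are an assumption.

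**3. One contrast under Bonferroni.** Family of six pairs (assumed): level 0.05/6 = 0.00833.

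- Noncentrality of the t-test: 0.8 × √(28/2) = 2.993, with 54 degrees of freedom.
- Critical t = 2.739, power = 0.602.

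**4. Bonferroni against Holm.** Simulation with 200,000 trials per setting, normal data, a one-way F gate at 0.05, then two-sample t-tests on six pairs:

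| Two tVNS arms against two controls | Bonferroni | Holm |
|---|---|---|
| 28 per group: mean power per tVNS-control contrast | 0.60 | 0.66 |
| 28: a given arm beats both controls | 0.44 | 0.52 |
| 28: all four contrasts | 0.26 | 0.37 |
| 28: at least one contrast | 0.90 | 0.90 |
| 34: mean power per contrast | 0.72 | 0.77 |
| 34: a given arm beats both controls | 0.58 | 0.66 |
| 34: all four contrasts | 0.40 | 0.52 |

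**5. Sensitivity.**

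- Family of only the four tVNS-control contrasts, 28 per group: mean power 0.66 against 0.76; all four 0.32 against 0.56.
- One arm differing from the other three, same f, six pairs: mean power 0.76 against 0.79 with 28 per group, and 0.86 against 0.88 with 34.
- Half the planned effect (f = 0.1), two against two, six pairs, 28 per group: mean power 0.114 against 0.124.

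**6. Familywise error, six pairs, 28 per group.**

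- All groups equal: 3.5% for both methods after the gate.
- Two against two at the planned effect: 1.7% Bonferroni, about 3% Holm.
- One against three: 2.2% to 2.3% Bonferroni, about 3.7% Holm.

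Both stay under 5%; Holm uses more of the allowance.

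**The case against.** The best defence is that nothing in the plan is wrong. Bonferroni controls the error it claims to control, the tests are labelled exploratory, the trial is sized on the interaction, and the article calls itself a pilot study. Bonferroni also has matching simultaneous confidence intervals, which Holm lacks in simple form. The gain depends on the measure: it is largest for joint results, about 5 points for a single contrast in the main scenario, and nil for finding at least one difference. All this stands and sets the priority. It does not remove the point, because section 2.6 states no other test of the tVNS-control contrasts.

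Two stronger readings are tempting, and neither is supported.

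- **That the plan corrects for multiplicity twice, because a significant ANOVA is required before the Bonferroni step.** At the planned effect the gate costs almost nothing: mean power per contrast is 60.3% without it and 60.2% with it. Nor does it make the pairwise correction redundant. With four groups, the F-test protects only the case where all are equal. Unadjusted t-tests after the gate give 9.1% to 12.3% familywise error when some but not all groups differ at the planned effect. The loss comes from Bonferroni's fixed divisor alone.
- **That the gate allows Shaffer's smaller divisors (3, 3, 3, 3, 2, 1), since at most three of six equalities can survive a rejected four-group F-test.** That logic needs the F-test and the t-tests to address the same means. The planned ANOVA has eight days, and a significant group-by-day interaction does not rule out equality of all groups on one particular day. With 28 per group, correlation 0.5, a 0.8 SD benefit on days 1 to 4 that vanishes in follow-up, and six pairs tested on day 8, familywise error on that day was 7.6% with Shaffer's divisors and 3.7% with Bonferroni or Holm.

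**Conclusion.** The point holds as an efficiency gain. Section 2.6 names a valid correction that Holm dominates at the same 5% familywise error. In the scenario closest to the article's own prediction, the gain is about 8 points for one arm beating both controls (0.44 to 0.52), 11 points for all four contrasts (0.26 to 0.37), and 5 to 6 points of mean power per contrast. It is about 2 to 3 points of mean power if one arm stands apart, and nothing for detecting at least one difference.

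These figures assume six pairs, balanced groups, normal data and pre/post change scores. The article does not state the family, and the planned model uses eight post-baseline days, so the exact sizes would change with those choices. The ranking would not: over any fixed family, Holm rejects at least what Bonferroni rejects. Priority is low and the change optional.

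**What to change.** In section 2.6, replace the Bonferroni correction of the post-hoc t-tests with Holm step-down adjustment over the same family of comparisons, and report the adjusted p-values. Keep the full family as Holm's starting divisor; do not reduce it on the strength of the preceding ANOVA.

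The cost is one phrase, with no new data, visits or patients. Step-down p-values have no simple matching simultaneous confidence intervals, so Bonferroni or unadjusted intervals should be shown beside them and labelled as such. An interval and its p-value may then occasionally disagree, which a sentence in the report can explain.

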
### 2.3. Outcome Measures

The intensity and magnitude of the baseline symptoms and primary (pain) and secondary (fatigue and health-related quality of life, sleep disorders, depression, physiological measures) outcome measures will be recorded by a validated Spanish version of the Brief Pain Inventory (BPI) [57] (pain intensity measure), the Patients’ Global Impression of Change (PGIC) [58] (restricted to pain intensity changes), a validated Spanish version of the revised Fibromyalgia Impact Questionnaire (FIQR) [59] (fatigue and health-related quality of life, as a secondary measure of general symptom improvement), the Pittsburgh Sleep Quality Index (PSQI) [60,61] (sleep measure), and the Beck Depression Inventory (BDI) [62,63,64,65] (depression measure). Additionally, heart rate variability (the high/low heartbeat ratio as an index of cardiac vagal regulation) and pro-inflammatory cytokine levels (TNF α, IL-1β, IL-6) will be recorded as secondary physiological outcome measures. Heart rate variability will serve as an indirect marker of the efficacy of vagal neuromodulation, at the level of its autonomic effects.

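### Heart rate variability and cytokines carry a treatment hypothesis, but the only analysis Section 2.6 specifies for them is within-group correlation, which cannot test it

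*Protocol article*

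**What the plan says.** **Hypothesis.** The Introduction of the protocol article expects pain and symptom benefit "in comparison with sham and axillary nerve stimulation controls", and continues that tVNS "secondarily will also normalize the autonomic (via heart rate variability) and immune (via pro-inflammatory cytokine levels) functions" thought to be disturbed in fibromyalgia.

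**Status of the markers.** Section 2.3 states that HRV and the cytokines TNF-α, IL-1β and IL-6 "will be recorded as secondary physiological outcome measures". It adds: "Heart rate variability will serve as an indirect marker of the efficacy of vagal neuromodulation".

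**Data collection.** Section 2.5 schedules HRV before and after each session. Blood is taken five times: before treatment, after 10 and 20 sessions, and 1 week and 1 month after the end.

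**Analysis.** The 4 × 8 ANOVA in Section 2.6 "will be used to analyze the scores of the outcome measures obtained in each of the questionnaires throughout the study". The baseline ANOVA lists BPI, FIQR, PGIC, PSQI and BDI. For HRV, Pearson's r is planned per tVNS group "to analyze possible correlations between vagal activity measures (heart rate variability) during the intervention and questionnaire scores"; the same sentence extends this to cytokine levels and outcome measures. Section 2.5 also says that HRV will be correlated with outcomes. It says that cytokines will be analysed as candidate markers of an anti-inflammatory effect, but names neither method nor comparator. Section 2.6 ends: "The critical level of significance for all statistical analyses will be set to" p < 0.05. Bonferroni correction is mentioned only for the post-hoc t-tests after the ANOVAs.

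**The concern.** The question set for HRV and cytokines is whether stimulation changes them. The analysis stated for them asks whether patients with higher or lower marker values also have higher or lower symptom scores. These are different questions. Within one arm, marker and symptoms can move together because of disease severity, natural course or placebo response, with no effect of stimulation on the marker. Conversely, stimulation can move the marker in every patient and leave no correlation.

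At stake is the mechanistic half of the trial's rationale. The sham and axillary arms allow a randomised test of whether tVNS alters vagal tone or inflammation, and the analysis as written does not use them for that purpose.

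**Working it through.** **1. The plan's own figure.** The sample size in Section 2.1 reproduces: non-centrality = N × m × f² / (1 − ρ) = 112 × 2 × 0.04 / 0.5 = 17.92, critical F(3, 108) = 2.689 (printed as 2.68), power 0.951. It concerns the BPI group-by-time interaction only and has no bearing on HRV or cytokines.

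**2. Could the ANOVAs cover the markers by implication?** No. Their wording restricts them to questionnaires. The 4 × 8 layout is four intra-intervention plus four follow-up measurements. Cytokines have five samples, one of them before treatment. HRV is recorded twice per session over 20 sessions, with no follow-up recording listed. Neither schedule fits.

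**3. What a within-group correlation can detect.** If treatment adds a constant δ to every patient's marker X, then corr(X + δ, Y) = corr(X, Y), so the test cannot see δ. A simulation shows the size of this: 20,000 runs, 34 patients per arm, two-sided 0.05. The documents give no SD or expected effect for HRV or cytokines, so the shifts are assumed.

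| Assumed shift in the active arm | Pearson test rejects, true r = 0 | Pearson test rejects, true r = 0.5 | Two-group t-test rejects |
|---|---|---|---|
| 0 SD | 5.3% | 87.7% | about 5% |
| 0.5 SD | 5.1% | 87.3% | about 53% |
| 0.8 SD | 5.0% | 87.7% | about 90% |

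The Pearson columns stay flat as the treatment effect grows. The planned test can be significant with no effect on the marker and null with a large one.

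**4. What the missing comparison could detect.** Each of the four analysis groups has 34 patients (sham pooled as 17 + 17), or 28 (112 / 4) before the dropout allowance. Power of a two-group comparison at assumed standardised differences, unadjusted for baseline:

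| Standardised difference | 34 v 34 | 28 v 28 |
|---|---|---|
| 0.5 | 0.53 | 0.45 |
| 0.6 | 0.68 | 0.60 |
| 0.7 | 0.81 | 0.73 |
| 0.8 | 0.90 | 0.84 |

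The comparison is informative for fairly large effects.

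**5. Number of correlations, as an illustration only.** Two verum tVNS groups × 5 questionnaires × 4 markers (HRV plus three cytokines) = 40 tests at one time pairing. If every null is true, 40 × 0.05 = 2 false positives are expected. If the tests were independent, the chance of at least one would be 1 − 0.95^40 = 0.87. They are not independent, so 0.87 is an upper illustration. The count doubles to 80 if the sham tVNS groups are included.

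**The case against.** The best defence is that this is a condensed article, and models for secondary biomarkers are often left to the full protocol or SAP. That would answer silence. Here the article does state an analysis for these outcomes, and that analysis does not match the hypothesis. What stands is a limit on wording: no between-group comparison is specified. A reader might infer that the markers will never be compared, or that the trial will be unable to say whether tVNS affected them. The documents do not support that, least of all for cytokines, where Section 2.5 leaves the method open.

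A reader might also infer that control-arm physiology is left out altogether. That is not established either. Section 2.5 names two control arms Sham atVNS and Sham ctVNS, so the reference in Section 2.6 to each tVNS group may include them. Separate correlations per group would still compare nothing between groups, and the axillary arm would remain outside.

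The comparator in the Introduction is attached to the analgesic and therapeutic effects and is not repeated for the physiological clause. Carrying it over is a reasonable reading rather than a literal one. Without it, a claim that treatment normalises a marker still needs a control.

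Finally, the Discussion calls the study a pilot, and Section 2.6 speaks only of possible correlations. Nothing in the text says that the authors will present them as proof of mechanism. This supports labelling them exploratory; it does not supply the missing test.

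**Conclusion.** The point holds in this form: Section 2.6 specifies only within-group correlations for HRV and cytokines, so the hypothesis that tVNS normalises them is not tested as written. The conclusion rests on the wording of the Introduction and Sections 2.3, 2.5 and 2.6, and on the fact that a correlation is unchanged by a constant shift. The simulated percentages depend on assumed shifts and correlations; the insensitivity to a constant shift does not. If the effect varied between patients, the correlation could change, but it would still not estimate a difference between groups.

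The 0.87 figure should not be read as the trial's false-positive risk. It assumes 40 independent tests and does not measure the main defect.

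This concerns secondary outcomes. The primary BPI analysis is untouched. The change should be made, but the trial's main conclusion does not hang on it.

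**What to change.** In Section 2.6:

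- Add a between-group comparison of HRV and of each cytokine, tVNS arms against sham and against axillary stimulation, at one pre-named time point such as the end of the 20 sessions, adjusted for the marker's own baseline.
- Label the Pearson correlations exploratory, say which groups they cover, and state that no mechanistic claim will rest on an uncorrected p < 0.05.
- Confirm that HRV and blood samples are taken in all arms. Section 2.5 and Figure 3 tie HRV recording to tVNS sessions, which leaves the axillary arm unclear.

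Transformation of cytokine values, choice of HRV summary and method of multiplicity control can be left to the SAP. The cost is some wording and a few extra models. If all arms are already measured, no new data collection is needed; if the axillary arm is not, recording there has to be added or that contrast dropped.

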## 3. Discussion

This study aims to explore the effects of multiple tVNS sessions on fibromyalgia symptoms. Because the vagus nerve modulates afferent pain signals to the central nervous system and the tone of the autonomic, immune, and emotional systems [19], the application of tVNS, a non-invasive low-intensity electric stimulation technique with potential to activate A- and B-fibers [75], might normalize the functions of vagal afferences, which seem to be pathologically altered in fibromyalgia [25], and thus reduce the characteristic symptoms of this disease, particularly muscular and generalized pain. Encouraging results have been reported for invasive vagal stimulation procedures in fibromyalgia treatment [31], but controlled clinical trials using non-invasive vagal stimulation are missing with respect to the effectiveness and safety of this neuromodulation option. The proposed study might shed light on the involvement of vagal activity and sympathetic–vagal balance in chronic pain and other symptoms of patients with fibromyalgia and also provide direct comparisons between two tVNS protocols in terms of effectiveness and safety. In particular, we hypothesize that this protocol of vagal neuromodulation is effective and safe for improving pain and other symptoms in these patients. The inclusion of a sham intervention condition is important to demonstrate the specificity of the therapeutic effectivity of this intervention. The inclusion of an active control condition, in which a nerve not related to fibromyalgia symptoms (the axillary nerve) is stimulated, will deliver further evidence about the specificity of the effects. The high number of intervention sessions (20 sessions, over 4 weeks) included in this stimulation protocol might serve to control for null effects of tVNS due to under-dosing.

The results of this intervention will help to elucidate if tVNS is a feasible method to induce clinically relevant analgesic effects in fibromyalgia patients (primary outcome measure). In addition, considering that the vagus nerve controls the autonomic nervous system and inflammatory signals [18,19,20], whose activity is apparently altered in fibromyalgia patients [25,27], other symptoms, including sleep and mood disorders, and quality of life (secondary outcome measures) could also benefit from this intervention. However, this study might face some limitations. First, high inter-individual variability in the fibromyalgia symptoms [76] might make it difficult to evaluate the efficacy of the treatment, despite the control of the baseline symptom state. Future multi-center studies with highly representative samples might be required to support the validity of the results of the envisaged pilot study. Preliminary results accomplished by this study may also be extended in future studies by the inclusion of other groups with chronic pain not primarily related to disturbances of the autonomic or immune systems, such as, for example, post-stroke pain, in which muscle pain symptoms are due to central alterations.

